### Immunogenicity

- Change from Baseline in T-cell and/or antibody response as measured using other exploratory measures of immune function. Such measures of humoral and T-cell responses may include (but are not limited to):
  - T-cell responses (IFN $\gamma$ , interleukin 2 [IL-2], tissue necrosis factor alpha [TNF $\alpha$ ] and other cytokine production by CD4 positive (+) or CD8+ T-cells as measured by intracellular cytokine staining (ICS).
  - Where responses to a whole pool of peptides are obtained, positive responses may be assessed with a matrix of peptides to give information on the breadth of the response and likely epitopes governing the responses.
  - Innate immune responses (e.g. number and function of dendritic cells).
  - Proportion and phenotype of T-cells measured by flow cytometry and MHC tetramer analysis.
  - Influence of HLA type on monitored immune response.
  - Change from baseline of T-cell receptor type
- Histological assessment of the nature of local tissue response at the site of vaccination.

## 4.3 Study Design

This is a randomized single or multi centre, double blind, placebo-controlled, parallel group pilot study to assess the safety and efficacy of a therapeutic HSV-2 DNA vaccine in HSV-2 positive adults. Subjects will be randomized to receive either COR-1 or placebo using a 3:1 allocation ratio. Treatment assignment to either COR-1 or placebo will be double-blinded. There will be 2 Groups of subjects. Group 1 will receive one injection into each forearm. Once this group has been fully allocated, Group 2 will commence recruitment. Group 2 will receive two injections to the one forearm.

There are two primary reasons for inclusion of the 2 placebo arms:

- To maintain the blind; and
- To describe any natural variation in viral shedding rates between the baseline shedding assessment pre- and post-administration of the placebo.

## 4.4 Dosing Regimens

All subjects will receive either 2 intradermal injections of 200 $\mu$ L, to the forearm(s) of either:

Group 1-

- Two injections each containing 500mcg of COR-1 with one injection in each arm (two injections in total);
- Two injections containing placebo with one injection in each arm (two injections in total).

Group 2-

- Two injections each containing 500mcg of COR-1 in the one arm; or
- Two injections containing placebo in the one arm;

Intradermal injections will be administered to the patient's forearms at 4 weekly intervals. Following this a 6 month booster will administered.

The comparison of one versus two arms is designed to test the effect of antigen presentation of vaccine encoded viral antigens occurring in one draining lymph node (2 administrations in one forearm) versus two draining lymph nodes (one administration to each forearm).

#### **4.5 Study Sites**

This is a single centre study but this may be revised during the course of the study subject to recruitment.

#### **4.6 Estimated Duration of the Study**

40 subjects plus up to 10 replacements will be recruited over a period of up to 6 months. The on-study period per subject is 48 weeks with a screening/ run in of approximately 9 weeks. It is anticipated that the duration of the study will be 18 months including 6months for recruitment and 12 months for clinical conduct, with a further 6 months for reporting.

## 5 SUBJECT POPULATION

### 5.1 Selection and Number of Subjects

Otherwise healthy subjects who have at least a 12 month history of having a genital HSV-2 infection with self-reported clinical occurrences of at least 3 and no more than 9 episodes in the 12 months prior to Screening will be selected to participate in the study. If the subject is currently on anti-viral therapy at the time of screening, the subject will need a self-reported recurrence rate of at least 3 and no more than 9 occurrences in the 12 months prior to initiating anti-viral therapy.

The nature of the study and the potential risks will be explained to all candidates. Written informed consent will be obtained from each subject prior to performing any screening procedures/assessments.

Following the Screening assessments, subjects who meet all of the inclusion and none of the exclusion criteria will be eligible to continue in the run-in phase of the study. Inclusion/exclusion criteria will again be assessed at Visit 5 prior to randomisation.

Sufficient numbers of subjects will be screened in order to randomize approximately 40 subjects with COR-1 or placebo in either one or two arms.

There will be no exemptions and subjects must satisfy all eligibility criteria in order to participate.

### 5.2 Inclusion Criteria

The criteria for entry into the study are:

1. Diagnosis of genital HSV-2 infection confirmed by positive HSV-2 serology or if negative a documented positive HSV-2 pathology result, AND positive PCR for HSV-2 during the Baseline Shedding Assessment prior to randomisation
2. A history of recurrent genital HSV-2 for at least 12 months AND a self-reported history of at least 3 and no more than 9 reported lesion occurrences in the 12 months prior to Screening or, if currently on suppressive therapy, in the 12 months prior to initiation of suppressive therapy.
3. Aged 18 to 50 years, inclusive.
4. Male or female. Women of child-bearing potential must be using two effective methods of contraception and agree to continue to do so from Screening, throughout Investigational vaccine/placebo dosing and for 28 days after the last dose of investigational vaccine/placebo.
5. Has voluntarily given written informed consent.

### 5.3 Exclusion Criteria

1. Birthmarks, tattoos, wounds or other skin conditions on the forearms which could reasonably obscure injection site reactions.
2. Inadequate venous access to allow collection of blood samples.
3. Female subjects who are breastfeeding and those of reproductive potential with a positive urine beta human chorionic gonadotropin ( $\beta$ -HCG) pregnancy test at either Screening or the Baseline Visit (Visit 5).
4. Received immunomodulating agents (including immunosuppressive agents, interferon or other immune or cytokine-based therapies), and/or systemic chemotherapeutic agents within 60 days of Screening or expected to receive these agents during the course of the study. Stable use asthma inhalers and topical corticosteroids are permitted. All medications will be documented and reviewed for acceptance by the Investigator or a medically qualified nominee.
5. Receiving medication known to have anti-HSV-2 activity within 7 days of the Baseline Shedding Assessment.
6. History of or active serious medical or psychiatric illness which, in the opinion of the Investigator, may impair the ability to provide written informed consent and would interfere with treatment, assessment, compliance with the protocol, or subject safety.

7. History of HSV-1 genital infection, ocular HSV infection, HSV-related erythema multiforme, herpes meningitis or encephalitis.
8. HSV-1 positive PCR result during the Baseline Shedding Assessment.
9. Laboratory blood values:
  - a) Haemoglobin <12.0 grams/decilitre (g/dL) for men and <11.0 g/dL for women
  - b) Neutrophil count <1000/mm^3
  - c) Platelet count <80,000/mm^3
  - d) Aspartate aminotransferase (AST) or alanine aminotransferase (ALT) >1.5 times the upper limit of normal (ULN)
  - e) Amylase >1.5 times ULN (unless serum lipase is >1.5 times ULN)
  - f) Subjects with an estimated creatinine clearance of <80 mL/minute (min)
  - g) INR > ULN
  - h) Hepatitis B surface antigen (HBsAg), Hepatitis C Virus (HCV) antibody or HIV antibody positive.
10. Subject has received any vaccine or investigational drug within 30 days prior to Visit 2, or is due to receive subsequent vaccines during the treatment period.
11. Subject has participated in the past in another clinical trial of a vaccination related to infection with HSV (unless it can be verified that the subject received placebo).
12. Any known or suspected allergies to the study drug or its constituents.
13. Subject has a compliance of less than 80% of swab sample collection during the Baseline shedding assessment i.e. immediately prior to randomisation.
14. Previous participation in this study or the previous COR-1 Phase I study.
15. Subject unwilling to abstain from blood donation during the course of the study.

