### 6.4.4 Electrocardiograms

The ECG recordings in this clinical trial will be performed by the Investigator or designated nominee. Repeat measurements will be performed if there are any clinically significant abnormalities observed or artifacts are present. All ECG recordings will be reviewed by the Investigator or medically qualified nominee who will document whether the tracing is normal or abnormal. If abnormal the Investigator or medically qualified nominee will document whether the abnormality is assessed as clinically significant or not.

The ECG recordings will be performed once the subject has been resting semi-supine for at least 10 minutes. The following parameters will be reported: QRS, QT, QTc, RR and PR intervals. The formula for calculating the corrected QT interval in respect to the heart rate will also be calculated using either Bazett or Fredericia formulas. If this isn't automatically calculated by the ECG machine, the following formulas will be used:

- Bazett's formula:  $QT / (RR)^{0.5}$   
[Observed QT interval divided by root of RR interval, in seconds]

- Fridericia's formula:  $QT / (RR)^{0.33}$

[Observed QT interval divided by cube root of RR interval, in seconds]

All tracings will be printed out and retained with the subject's source notes. Any clinically significant out of range results will be recorded in the subject's CRF and the subject will be excluded from the study.

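### Exclusion 6 joins its consent and safety conditions with 'and', so read literally it does not exclude a serious illness judged unsafe unless consent may also be impaired

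*Protocol*

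**What the plan says.** Exclusion 6 in section 5.3 of the protocol opens with "History of or active serious medical or psychiatric illness which, in the opinion of the Investigator" and goes on to require that the illness "may impair the ability to provide written informed consent and would interfere with treatment, assessment, compliance with the protocol, or subject safety". The synopsis version differs only in adding that the active illness is current; the connective is the same.

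Section 5.1 makes the listed criteria the test of eligibility: "subjects who meet all of the inclusion and none of the exclusion criteria will be eligible to continue in the run-in phase of the study". It adds: "There will be no exemptions and subjects must satisfy all eligibility criteria in order to participate". The same section describes the people to be selected as "Otherwise healthy subjects who have at least a 12 month history of having a genital HSV-2 infection", and the primary objective (synopsis and section 4.1) also names otherwise healthy subjects. That phrase is not defined and is not one of the numbered criteria.

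Consent appears separately as Inclusion 5: "Has voluntarily given written informed consent". Sections 5.1 and 6.3.1.1 place consent before every screening procedure.

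**The concern.** A criterion of this kind normally does two jobs. It keeps out people who cannot properly consent, and it keeps out people whose illness would make participation unsafe or the data hard to interpret. Here the second job is conditional on the first. An Investigator who thinks that a subject's illness would endanger that subject, but who has no doubt about consent, cannot point to Exclusion 6 as the reason for refusal.

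Two things are at stake. The first is protection of participants in a Phase I/IIa study of a DNA vaccine. The second is classification: the per-protocol set in section 11.1.1 requires compliance with the inclusion and exclusion criteria. A subject with a serious illness that the Investigator thought unsuitable would count as compliant on the literal text and as non-compliant on the probable intent.

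**Working it through.** No arithmetic applies, so the check is a reading of the wording against the rest of the eligibility text.

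**Step 1. Structure of the criterion.** One relative clause carries two verbs. Limb A is that the illness may impair consent. Limb B is that it would interfere with any of four things: treatment, assessment, compliance or subject safety. The 'or' separates only the items inside limb B; A and B are joined by 'and'. Exclusion 4 in the same list shows that the authors had another form available for alternatives: "and/or systemic chemotherapeutic agents within 60 days of Screening".

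**Step 2. The four cases.**

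| A: may impair consent | B: would interfere or endanger | As written (A and B) | With 'or' |
|---|---|---|---|
| Yes | Yes | Excluded | Excluded |
| No | Yes | Not excluded | Excluded |
| Yes | No | Not excluded | Excluded |
| No | No | Not excluded | Not excluded |

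The second row is the important one.

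**Step 3. How often limb A can be met.** Everyone being screened has already given written consent, and Inclusion 5 requires it. Limb A is therefore seldom met among the people to whom the criterion is applied. The text says 'may impair', which is wider than 'impairs', so the limb is not empty. But limb B has no effect without it.

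**Step 4. The other numbered exclusions.** They cover forearm skin, venous access, pregnancy and breastfeeding, immunomodulators and chemotherapy (4), anti-HSV-2 medication (5), specified HSV history and HSV-1 results (7, 8), laboratory limits with HIV and hepatitis (9), vaccines and investigational drugs (10), earlier trials (11, 14), allergy (12), swab compliance (13) and blood donation (15). Each is specific. None gives a general ground based on illness or on the Investigator's view of safety. For example, a subject with a malignancy whose chemotherapy ended more than 60 days before Screening falls outside Exclusion 4. If the Exclusion 9 limits are met, no other item on the list addresses that illness.

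**Step 5. Provisions outside the list.**

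| Provision | What it reaches | General exclusion for serious illness? |
|---|---|---|
| Section 6.4.4, ECG | "Any clinically significant out of range results will be recorded in the subject's CRF and the subject will be excluded from the study" | No, ECG findings only |
| Sections 6.3.1.1 and 6.4.2, screening examination | Body systems examined to determine eligibility | No, the rule to apply is not stated |
| Section 5.4, safety documents | Investigator must consult the Investigator's Brochure or equivalent on safety aspects of eligibility | None stated in the protocol |
| Exclusion 4, expected use | Subjects expected to need immunomodulators during the study | No, drug-based |
| Section 10.2, withdrawal | Concurrent illness after entry | No, not an entry rule |

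**Step 6. Comparison with the stated population.** The objective and section 5.1 call for otherwise healthy subjects. Exclusion 6 is the only numbered criterion broad enough to give effect to that, and row 2 of the table shows that its literal wording does not.

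**The case against.** The strongest reply is that the intent is plain and the protocol has other safeguards. Section 5.1 says that otherwise healthy subjects will be selected. Section 5.4 obliges the Investigator to check safety documents when judging eligibility. The screening examination is done to determine eligibility, and a clinically significant ECG finding excludes outright. An Investigator reading these together is unlikely to enrol someone with dangerous disease. This stands as far as it goes: it makes actual harm less likely and marks the fault as one of drafting. It does not supply the missing rule, because none of these provisions says that serious illness excludes.

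Three stronger readings are tempting, and the documents do not support them.

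- A reader might infer that seriously ill subjects who can consent meet no barrier at all. The partial gates above contradict that. The Investigator's Brochure is also not at hand, so its contraindications cannot be assumed to be silent.
- A reader might infer that the sentence on exemptions in section 5.1 forces such subjects in. It bars waivers for people who fail a criterion; it does not oblige enrolment of everyone who passes. Passing makes a subject eligible to continue.
- A reader might infer that background fatigue, myalgia or arthralgia from such illness would be counted in the primary safety endpoint. Section 8.2 leaves out pre-existing conditions that do not worsen, and section 11.1.4 bases the primary adverse event analysis on events that are new or worse from first dosing. Stable symptoms would not count.

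**Conclusion.** The point holds as a defect in an operative eligibility rule. As written in both places, Exclusion 6 does not exclude a serious illness that the Investigator judges unsafe or disruptive unless the illness may also impair consent. No other numbered criterion supplies a general illness or safety ground, and the result conflicts with the otherwise healthy population in the objective and section 5.1. Since the synopsis and section 5.3 share the wording, neither corrects the other.

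Its size cannot be put in numbers: the protocol gives no frequency of serious illness among candidates. The share that one subject forms of a treatment group would not measure it, because that share is the same for any feature of any subject. No sample-size, power or error-rate figure is affected; section 11.1 sets the sample size on practical grounds and makes no power claim.

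The conclusion rests on a literal reading of 'and', and on taking 'otherwise healthy' as evidence that either limb was meant to suffice. The change is worth making for participant protection and clear classification, but it does not call the design into question.

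**What to change.** Reconcile Exclusion 6 with the otherwise healthy population in both the synopsis and section 5.3. Replace the 'and' between the consent limb and the interference limb with 'or' (or 'and/or'), leaving the Investigator's opinion as the standard and the list inside the second limb unchanged. Either limb then excludes.

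The cost is one word in two places. Because it alters a subject selection criterion, section 12.1.5 calls for consultation between sponsor and Investigator and for ethics committee approval before it takes effect. A few more candidates may be screened out on the Investigator's judgement. No assessment, analysis or sample-size statement has to change.

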| Exclusion criteria: | 
 
1. Birthmarks, tattoos, wounds or other skin conditions on the forearms which could reasonably obscure injection site reactions.
 
2. Inadequate venous access to allow collection of blood samples.
 
3. Female subjects who are breastfeeding and those of reproductive potential with a positive urine beta human chorionic gonadotropin (<math>\beta</math>-HCG) pregnancy test at either Screening or the Baseline Visit (Visit 5).
 
4. Received immunomodulating agents (including immunosuppressive agents, interferon or other immune or cytokine-based therapies), and/or systemic chemotherapeutic agents within 60 days of Screening or expected to receive these agents during the course of the study. Stable use asthma inhalers and topical corticosteroids are permitted. All medications will be documented and reviewed for acceptance by the Investigator or a medically qualified nominee.
 
5. Receiving medication known to have anti-HSV-2 activity within 7 days of the Baseline shedding assessment.
 
6. History of or currently active serious medical or psychiatric illness which, in the opinion of the Investigator, may impair the ability to provide written informed consent and would interfere with treatment, assessment, compliance with the protocol, or subject safety.
 
7. History of HSV-1 genital infection, ocular HSV infection, HSV-related erythema multiforme, herpes meningitis or encephalitis.
 
8. HSV-1 positive PCR result during the Baseline Shedding Assessment.
 
9. Laboratory blood values: 
 
a. Haemoglobin <12.0 grams/decilitre (g/dL) for men and <11.0 g/dL for women
 
b. Neutrophil count <1000/mm^3
 
c. Platelet count <80,000/mm^3
 
d. Aspartate aminotransferase (AST) or alanine aminotransferase (ALT) >1.5 times the upper limit of normal (ULN)
 
e. Amylase >1.5 times ULN (unless serum lipase is <math>\leq</math>1.5 times ULN)
 
f. Subjects with an estimated creatinine clearance of <80 mL/minute (min)
 
g. INR > ULN
 
h. Hepatitis B surface antigen (HBsAg), Hepatitis C Virus (HCV) antibody or HIV antibody positive.
 
 
 
10. Subject has received any vaccine or investigational drug within 30 days prior to Visit 2, or is due to receive vaccines
 
 |

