#### 6.4.5 Blood and urine samples for laboratory tests

Blood and urine will be collected at Screening (Visit 1), Baseline (Visit 5), and scheduled clinic Visits 7, 9, 16 and 22. Blood will be collected at scheduled clinic Visits 6, 7, 8, 9, 11, 12, 15, 16, 17, 18 and 22. Samples for laboratory tests should be collected within the visit window. Detailed instructions on the handling and processing of specimens are located in the Study Reference Manual. The following will be collected at the times specified in Section 6.3.

|                                 |                                                                                                                                                                                                                                                                                                                                                                |
|---------------------------------|----------------------------------------------------------------------------------------------------------------------------------------------------------------------------------------------------------------------------------------------------------------------------------------------------------------------------------------------------------------|
| Haematology:             | Haemoglobin, haematocrit, red blood cell (RBC) and RBC morphology, white blood cell and differential white blood cell count, platelet count,                                                                                                                                                                                                            |
| Chemistry:               | Sodium, potassium, chloride, bicarbonate, BUN, creatinine, total protein, albumin, lipase, phosphorus, AST, ALT, GGT, alkaline phosphatase, total bilirubin, glucose, CPK, calcium, uric acid, GFR*                                                                                                                                                     |
| Coagulation:             | Prothrombin time (PT), partial thromboplastin time (PTT), and International Normalized Ratio (INR).                                                                                                                                                                                                                                                     |

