## 8.5 Clinical Laboratory Abnormalities and Other Abnormal Assessments as AEs or SAEs

All laboratory values must be reviewed by the Investigator. Given that all laboratory data are collected and statistically analysed according to their respective toxicity gradings, laboratory abnormalities that occur without related clinical symptoms and signs should generally not be recorded as an AE unless they are considered clinically significant by the Investigator. Where possible, the overall diagnosis rather than the laboratory abnormality should be recorded on the CRF. This will avoid duplication of laboratory abnormalities in both the CRF and laboratory reports. Abnormal laboratory results that are of clinical significance should be reviewed by the Medical Monitor.

Any laboratory test result that meets the criteria for a SAE (refer to Section 9.3) should be recorded as an AE, the AE page of the CRF completed and a SAE form also completed in order for the Sponsor to collect additional information about that abnormality, including information regarding relationship to study product or other causes, any action taken and resolution.

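### Exclusion 9(e) is worded in opposite ways in the synopsis and in Section 5.3, and amylase, which triggers it, is not in the scheduled chemistry panel

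*Protocol*

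**What the plan says.** Exclusion 9(e) appears twice in the protocol. Section 5.3 reads "Amylase >1.5 times ULN (unless serum lipase is >1.5 times ULN". The synopsis has the same amylase threshold, but its waiver reads "unless serum lipase is \leq 1.5 times ULN", that is, lipase at or below 1.5 times ULN.

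Section 5.1 leaves no discretion: "There will be no exemptions and subjects must satisfy all eligibility criteria in order to participate".

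Section 6.4.5 sets out the chemistry panel as a closed list: "Sodium, potassium, chloride, bicarbonate, BUN, creatinine, total protein, albumin, lipase, phosphorus, AST, ALT, GGT, alkaline phosphatase, total bilirubin, glucose, CPK, calcium, uric acid, GFR". Lipase is in it and amylase is not. The schedule in Table 1 shows chemistry as a single row and adds no further analytes. Amylase otherwise appears only in the Appendix 2 grading table, in the row for pancreatic enzymes.

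**The concern.** An eligibility rule should give one answer for one set of results, and those results should come from tests that the protocol schedules. Criterion 9(e) appears to fail on both counts. If so, a candidate's eligibility could depend on which page the site consults, or the criterion could go unapplied without anyone noticing.

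There is also an effect on the analysis. Section 11.1.1 limits the per-protocol set to subjects who comply with the inclusion and exclusion criteria. A subject with raised amylase would comply under one wording and deviate under the other, so membership of that set would be undefined for that subject.

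**Working it through.** No sample size, power or error rate is involved. The check is one of logic, followed by a comparison of the criterion with the panel.

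**Step 1: the two rules.** Let A mean amylase above 1.5 times ULN, and L mean lipase above 1.5 times ULN.

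- Synopsis: exclude if A, unless not L. This is the same as exclude if A and L.
- Section 5.3: exclude if A, unless L. This is the same as exclude if A and not L.

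| Amylase above 1.5 times ULN | Lipase above 1.5 times ULN | Synopsis | Section 5.3 |
|---|---|---|---|
| No | No | Not excluded | Not excluded |
| No | Yes | Not excluded | Not excluded |
| Yes | No | Not excluded | Excluded |
| Yes | Yes | Excluded | Not excluded |

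The rules agree in both rows without raised amylase and disagree in both rows with it. No candidate with raised amylase gets the same answer from the two wordings, and no reading satisfies both.

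**Step 2: can either rule be applied?** Both rules start from A. The Section 6.4.5 list contains 20 items, counting GFR; lipase is among them and amylase is not. L can be determined at screening and A cannot. Without A, neither rule can be evaluated.

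**Step 3: how the two defects interact.** Adding amylase to the panel without settling the wording makes the contradiction operative. Settling the wording without adding amylase leaves a clear rule that the scheduled tests cannot check. Each repair is incomplete without the other.

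**Step 4: the remaining numeric limits.** These were compared with the Appendix 2 bands for context only.

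| Limit in exclusion 9 | Lowest (for AST/ALT, highest) values admitted | Worst Appendix 2 grade admitted |
|---|---|---|
| Platelets below 80,000/mm³ | 80,000–99,000 | 3 |
| Neutrophils below 1,000/mm³ | 1,000–1,499 | 2 |
| Haemoglobin, men, below 12.0 g/dL | 12.0–12.4 | 2 |
| Haemoglobin, women, below 11.0 g/dL | 11.0–12.0 | 1 |
| AST or ALT above 1.5 times ULN | 1.1–1.5 times ULN | 1 |

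INR and creatinine clearance have no row of their own in Appendix 2. Three limits therefore admit subjects already at Grade 2 or 3.

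**The case against.** The best reply on 9(e) is that its two faults do not bite together. If amylase is never measured, the reversed wording cannot send two candidates different ways; it matters only where a site knows an amylase value from elsewhere. Eligibility is also settled before randomisation, so the arms are not biased against each other. Both points are correct and limit the consequences. They do not rescue the criterion, which is either unverifiable or contradictory depending on what the site happens to know.

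A reader might infer more in two directions.

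- **That exclusion 9 as a whole cannot be applied.** The documents do not support this. Items (a) to (d) and (f) to (h) can be applied as written.
- **That low baseline counts will be reported as vaccine toxicity.** The starting point would be Section 8.5, which says that "all laboratory data are collected and statistically analysed according to their respective toxicity gradings", together with the bands in Step 4. But that clause explains why isolated laboratory values are generally not recorded as adverse events; it does not set a tabulation. Section 11.1.5 allows for summaries of change from baseline and leaves the detail to the SAP, which is not at hand. Sections 8.2 and 11.1.4 keep findings that do not worsen out of the adverse event and treatment-emergent counts. The guidance reproduced in Appendix 2 says that its tables are not eligibility criteria, so a limit such as "Haemoglobin <12.0 grams/decilitre (g/dL) for men and <11.0 g/dL for women" does not contradict the grading scale. Laboratory values are a safety endpoint in Section 11.1.3 but are not named in the primary endpoint in Section 4.2.

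**Conclusion.** The point stands for 9(e). The synopsis and Section 5.3 give opposite eligibility for every candidate with amylase above 1.5 times ULN, and the scheduled panel does not measure amylase. This follows from the text alone and needs no numerical assumption. It assumes only that Section 6.4.5 is the full chemistry list; the Study Reference Manual, which is not shown, might add to it.

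How many subjects are touched is unknown. The protocol gives no frequency of raised amylase, and in otherwise healthy adults aged 18 to 50 the number may be small or zero. The effect is on safety screening and on membership of the per-protocol set, not on the comparison of arms. It is worth correcting because the rule is absolute, an SAP cannot repair it, and the repair is cheap.

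The overlap of the platelet, neutrophil and male haemoglobin limits with Grades 3, 2 and 2 is a side note and not an error in the protocol.

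**What to change.** 1. The sponsor's medical lead should reconcile the two wordings of 9(e) so that the synopsis and Section 5.3 read the same. Which wording is intended is a clinical decision and is not proposed here.
2. In the same amendment, make Section 6.4.5 and the criterion match: either list amylase for screening or restate the criterion using only analytes that are measured.
3. Optional: if laboratory results are tabulated by Appendix 2 grade, show each post-dose grade against that subject's Day 0 grade, for example as a shift table. The SAP may already do this.

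Items 1 and 2 cost a wording change with ethics committee submission and, if amylase is kept, one more analyte on the blood already drawn at Visit 1. Item 3 uses data already scheduled, since haematology and chemistry are taken on Day 0 before the first injection.
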